## **12.8 Interim analysis**

### **12.8.1 Rationale/reason for interim analysis**

Sample size determination is based on hypothetical positive response rates of not less than 80% and not more than 60% in the treatment and placebo group, respectively (Paragraph 12.3). These assumptions stem from information related to vaccine trials and observational studies conducted both in Italy and South Africa. These studies are now completed and have provided additional information. In particular, data from the studies in Italy indicate about 18% of anti-Tat Ab positive subjects on ART vs 28% positive subjects in South Africa (ISS OBS T-004, ClinicalTrials.gov identifier: NCT01359800). In addition, a longitudinal observational study completed in Italy (ISS OBS T-002, ClinicalTrials.gov identifier: NCT01024556) indicate an anti-Tat seroconversion of 9%. Therefore, the cumulative rate of anti-Tat seroconversion in the placebo group of the present study is expected not to exceed 40%, which is lower than what was indicated in the clinical protocol (60%) It is therefore necessary to re-evaluate the sample size upon interim evaluation of the data.

The interim analysis will be conducted only if approved before the 200 participants foreseen by the protocol are enrolled into the study. All participants that have signed the informed consent form and have been vaccinated at least once by the time of the conclusion of the interim analysis will complete the study as per protocol, irrespective of sample size re-evaluation.

### **12.8.2 Statistical analysis and population**

At least 50% of the original planned population will be included in the interim analysis ( i.e. at least 100 subjects). At the time of the interim analysis, data for the humoral immune response to Tat will be used to re-calculate the sample size. “Responders” will be defined using the same criteria as described in section 12.6. Data for all subjects who were randomised and who received at least 2 vaccinations will be included in this analysis. No other data will be analysed for the purpose of the interim analysis.

### **12.8.3 Preserving of blindness**

An independent statistical vendor, who will not be involved in the final statistical analysis, will perform the sample size re-calculation.

### **12.8.4 Timing of interim analysis**

The sample size re-calculation will be performed when at least 100 subjects have received at least 2 vaccinations, i.e., have completed at least the Week 8 assessments (Visit 6).

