## **2.2 Rationale for the Selection of Vaccine Dosage and Schedule of Vaccination**

Although the Tat vaccine was shown to be safe and highly immunogenic at all doses, more intense humoral immune responses were observed with 7.5 and 30  $\mu$ g doses of Tat as compared to the 15  $\mu$ g dose and more persistent responses were induced by the 30  $\mu$ g dose. Further, Tat-specific cellular responses, particularly IL-4 and lymphoproliferation, were more frequent in subjects randomized to intradermal administration.

With regard to the vaccination schedule, in the Phase I trials the anti-Tat antibody titres peaked after three vaccinations. In the ongoing phase II clinical trial, the administration of three intradermal vaccinations with 30  $\mu$ g of Tat were associated with a significant increase of CD4+ T cell and B cell numbers, as well as with the recovery of regulatory T cells while a concomitant decrease of CD25+/CD4+ T cells and CD38+/CD8+ T cells was observed (Ensoli et al, PLoS ONE 2010). Based on this data and considering that all doses were equally well tolerated and safe, three intradermal vaccinations with 30  $\mu$ g of Tat was chosen as the optimal dosage and regime for the present clinical trial. This choice also offers additional benefits since it is less expensive, is administered without adjuvant and may favour better compliance to the treatment.

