### 4 STUDY DESIGN

*The study is a phase II, randomized, double-blinded, placebo controlled, clinical trial to evaluate the immunogenicity and safety of a therapeutic, biologically active HIV-1 Tat protein vaccine. HIV-1 positive volunteers will be recruited and screened. Volunteers will be eligible to participate based on the inclusion and exclusion criteria described in Section 6.1 and 6.2.*

*After a screening period of up to 35 days, the study duration will be 48 weeks, including an 8 week treatment phase (during which 3 vaccinations will be administered at 4-week intervals) and a 40 week follow-up phase.*

*This study will be conducted at 1 clinical site in South Africa. 200 Subjects will be randomized in a 1:1 ratio to one of the two treatment groups in accordance with the randomisation schedule detailed in section 5.6*

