**DAY 56: 3rd Vaccination (Day 56 +7 days)**

**Prior to the vaccine administration:**

- Physical examination including weight
- Vital signs after 5 minutes in a resting position (seated blood pressure, heart rate, respiratory rate and axillary body temperature)
- Concomitant medication and adverse event review
- Urine dipstick pregnancy test (for females of child-bearing potential only)
- CD4+ T cell counts
- HIV-1 plasma viraemia
- Anti-Tat antibodies (IgM, IgG, IgA)
- Immunological & Virological sample collection and storage.

Note: If the subject has a body temperature  $\geq 37.5$  °C or in the investigator's opinion, an acute illness, DO NOT VACCINATE; re-schedule the vaccination visit within the specified window period i.e. Day 56 + 7 days.

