### 12.3 Sample Size Determination

To evaluate the humoral immune response to vaccination, “responders” will be defined as those vaccinated subjects that develop an immune response above a specific cut-off level.

If positive response rates are 80% for the Tat vaccine group and 60% for the placebo group, with alpha set at 0.05 (2-tailed), a sample size of 91 per group will have 80% power of showing statistical significance ( $p < 0.05$ ). The assumed response rate for the Tat vaccine group is based on the results of phase I and ongoing phase II studies (Fleiss J.L. Tytun A., Ury S.H.K., A simple approximation for calculating sample sizes for comparing independent proportions, Biometrics, 1980).

Sample size was calculated using nQuery Advisor® software, version 6.01.

It is anticipated that approximately 10% of subjects will not complete the study. Therefore, a total of 200 subjects will be enrolled to ensure that 91 subjects per arm complete the study.

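### The sample-size re-calculation can use antibody responses from as early as Week 8, before the third dose, so the interim rates do not estimate the rates that the final comparison will use

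*Protocol*

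**What the plan says.** **Trigger.** Section 12.8.4 times the re-calculation "when at least 100 subjects have received at least 2 vaccinations, i.e., have completed at least the Week 8 assessments (Visit 6".

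**Data used.** Under 12.8.2, interim responders "will be defined using the same criteria as described in section 12.6". That section gives titre cut-offs (IgM 25, IgG 100, IgA 25) and names no visit or window. Section 12.8.2 neither restricts the interim data to a common visit nor projects them to a later one. It uses no data other than the humoral response.

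**Sampling.** In section 6.7, the Day 56 (Visit 6) anti-Tat sample is listed under "Prior to the vaccine administration". Further samples follow on Days 84, 112, 140, 168 and 336.

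**Final comparison.** Section 3 sets the objective as the immunogenicity of three doses. Section 8.1 compares induction, magnitude and persistence of the response to the schedule. The synopsis places the final analysis after all subjects have completed the study. Section 12.8.1 describes the expected placebo rate as a cumulative seroconversion rate of at most 40%. Section 2.2 notes that "in the Phase I trials the anti-Tat antibody titres peaked after three vaccinations".

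**Original sizing.** Section 12.3 assumes 80% against 60% and states that "a sample size of 91 per group will have 80% power of showing statistical significance".

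**The concern.** The re-calculation exists because the sponsor now doubts the 60% placebo assumption and expects 40% or less (12.8.1). To settle that, the interim rates must estimate the same quantity as the final rates. As timed, they do not.

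- A subject who has only reached Visit 6 contributes a response to two doses.
- That subject also contributes 8 weeks of natural seroconversion, while sampling runs to Week 48.
- Earlier entrants contribute more, so the pooled interim rate depends on how fast recruitment went.

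A low interim placebo rate therefore cannot be told apart from incomplete follow-up. If placebo conversion is cut short, the gap between arms looks too wide and the new sample size is too small. If the vaccine response is incomplete before the third dose, the gap looks too narrow and the new size is too large. Recruitment closed early on such a figure is hard to reopen.

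**Working it through.** **1. Reproduce the stated sample size.** Inputs from 12.3: 80% against 60%, two-sided 5%, 80% power. Fleiss formula with continuity correction, where p̄ is the mean of p1 and p2:

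- m = [1.960·√(2p̄(1−p̄)) + 0.842·√(p1(1−p1) + p2(1−p2))]² / (p1−p2)²
- n = (m/4)·[1 + √(1 + 4/(m·|p1−p2|))]²

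| Rates | m | n per arm |
|---|---|---|
| 80% v 60% | 81.2 | 90.9, so 91 (as stated) |
| 80% v 40% | 22.3 | 27.1, so 28 |

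The method matches the protocol's, and the answer is very sensitive to the placebo rate.

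**2. What a 60% placebo rate looks like at the interim.** Assumptions: Week 48 is the end of the final window, and placebo conversion has a constant hazard, so P(t) = 1 − (1 − P48)^(t/48).

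- At Week 8 exactly: 1 − 0.4^(8/48) = 1 − 0.858 = 14.2%.
- Averaged over follow-up spread evenly from 8 to 48 weeks: 1 − (0.858 − 0.400)/[(40/48)·ln 2.5] = 1 − 0.458/0.764 = 40.0%.

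The second figure treats conversion as seen continuously. With no sample between Day 168 and Day 336, the observed rate would be somewhat lower.

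**3. What the re-calculation returns.** With the vaccine rate at 80% and placebo appearing as 40%, the formula gives 28 per arm, against the 91 needed for 80% v 60%. The apparent 40% equals the ceiling that 12.8.1 already expects, so it would look like confirmation.

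**4. How small the trial could become.** Section 12.8.1 keeps in everyone vaccinated by the end of the interim, so the size cannot fall to 28 per arm.

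- The 100 interim subjects alone give 50 per arm.
- Even entry of 100 subjects over 40 weeks is 2.5 per week. Another 8 × 2.5 = 20 would be dosed while the last of the 100 reaches Week 8, giving about 60 per arm.

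Exact power of the uncorrected chi-square test, two-sided 5%, vaccine rate 80%:

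| True placebo rate | 50 per arm | 60 per arm |
|---|---|---|
| 60% | 59.5% | 68% |
| 50% | 89.5% | 94% |
| 40% | 99% | above 99% |

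On the continuity-corrected basis that yields 91, power at 50 per arm for 80% v 60% is about 50%.

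**5. The other direction.** Suppose the final truth is 80% v 40% (28 per arm). Assumed interim rates of 60% v 30% return 49 per arm, and 50% v 30% return 103. The protocol gives no two-dose responder rates, so these are scenarios only.

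**The case against.** Much of the case on the other side is sound.

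- **Week 48 is not stated.** A reader might infer that the responder endpoint is any response up to Day 336. Sections 8.1 and 12.6 give no window, and a statistical analysis plan that is not shown may supply one. Week 48 rests on the sampling schedule, the word cumulative in 12.8.1, the mention of persistence in 8.1 and the timing of the final analysis. The mismatch survives this: any window that uses samples after the third dose differs from a Visit 6 rate, and 12.8.4 and 12.8.2 themselves fix the trigger and the data.
- **Three doses are not required for analysis.** Sections 12.4 and 12.8.2 both admit subjects with two doses. That settles who is counted, not when they are measured.
- **Section 2.2 concerns titres.** It says nothing about the share of subjects above the cut-offs after two doses, so the size of any vaccine-arm shortfall is unknown.
- **An answer of 11 per arm is tempting but unsupported.** The formula returns it for 80% v 14.2%, but that needs every interim subject to be exactly at Week 8. The trigger says at least Week 8, and entry is staggered.
- **A reader might conclude that the 80% power is lost.** That follows only if the new size comes out too small and the true placebo rate is near 60%, a rate the sponsor no longer expects. At 40% or 50%, the subjects already enrolled suffice.

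**Conclusion.** The mismatch is real and sits in the stated rule. The re-calculation uses rates of mixed follow-up, some after two doses only, that do not estimate the rates in the final comparison. The direction of the error is undetermined.

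The worst case is a final placebo rate near 60%: the formula can return 28 per arm where 91 are needed, and the trial could close at 50 to 60 per arm with about 60% to 68% power. This rests on a constant placebo hazard, an 80% vaccine rate, even entry, and Week 48 as the end of the window. If the sponsor's expectation of at most 40% holds, stopping early does little harm.

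This should be fixed, but it does not by itself undermine the trial. Confidence is moderate, because the responder window has to be inferred.

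**What to change.** - **12.6 and 12.8.2:** state one responder window that ends at an existing visit after the third dose, and use only samples within it at both interim and final.
- **12.8.4:** trigger the re-calculation when 100 subjects have completed that visit. Visit 8 (Day 84) is the earliest candidate.
- **If the endpoint stays cumulative to Week 48:** project the interim rates to Week 48 by a method fixed in advance. A later trigger alone is not enough. With follow-up spread evenly over 12 to 48 weeks, a true 60% still appears as 1 − (0.795 − 0.400)/[(36/48)·ln 2.5] = 42%.
- **12.3:** re-state the planning rates for whichever window is chosen.

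**Cost.** The change needs protocol wording and an interim at least about four weeks later (Day 84 instead of Day 56), with more subjects enrolled before it. At the illustrative 2.5 entries per week, that is about 10 more. A window closing at Day 84 also drops later samples from the responder definition, so it is one option rather than the obvious choice. Persistence would then need its own summary.

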### **12.8.5 Adjustments to Type 1 error**

Since no formal treatment group comparison will be performed on the humoral immune response data, it will not be necessary to adjust for any inflation of the overall Type 1 error rate.

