| Study Population:    | A total of 200 subjects will be randomized into 2 treatment arms in a 1:1 ratio:
Group A: 3 intradermal administrations of Tat (30 µg) vaccine
Group B: 3 intradermal administrations of placebo                                                                                                                                                                                                                                                                                                                                                                                                                                                                                                                                                                                                                                                                                                                                                                                                                                                                                                                                                              |
| Inclusion Criteria:  | 
 
1. Male and female volunteers aged 18-45 years (inclusive)
 
2. Anti-Tat antibody negative
 
3. HIV-1 infected individuals currently receiving treatment with ARVs
 
4. Chronically suppressed HIV-1 infection as indicated by a HIV-1 plasma viraemia < 400 copies/ml and a CD4+ T cell count ≥ 200 cells/µl at screening, and documented at least once during the 12 month period prior to screening, irrespective of the pre-ARV CD4 nadir.
 
5. Negative pregnancy test for females of childbearing potential (not sterilized and still menstruating or within 1 year of the last menses) to be performed during the screening phase and immediately before each vaccination, and use of an acceptable method of contraception (double barrier methods, combined oral contraceptives, injectable contraceptives or intra-uterine devices) for at least 3 weeks prior to the first vaccination and for the duration of the study.
 
6. Has provided written informed consent.
 
7. Agrees to stay in contact with the research site for the duration of the study
 
 |

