### 12.6 Primary Endpoint Analysis

*To evaluate the **humoral immune response** to vaccination, “responders” will be defined as those vaccinated subjects that develop an immune response greater than the following levels:*

- *Anti-Tat IgM titers  $\geq 25$*
- *Anti-Tat IgG titers  $\geq 100$*
- *Anti-Tat IgA titers  $\geq 25$*

*The percentage of responders will be compared between active and placebo groups using the Chi-Square test. Additionally, geometric mean antibody titers (GMT) will be calculated and compared between treatment groups by using a t-Test for unpaired data.*

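### Section 12.8.5 waives Type I error adjustment for a reason that does not protect the level: without an interim test, alpha still exceeds 5% if the trial is re-sized on responder rates by arm

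*Protocol*

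**What the plan says.** Protocol section 12.3 sizes the trial from two arm rates: "If positive response rates are 80% for the Tat vaccine group and 60% for the placebo group", and "with alpha set at 0.05 (2-tailed), a sample size of 91 per group will have 80% power of showing statistical significance". The synopsis plans 200 subjects, 1:1. Section 12.6 fixes the final test: "The percentage of responders will be compared between active and placebo groups using the Chi-Square test". Section 12.5 sets it at 5%, two-tailed.

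Section 12.8.1 explains the interim. The placebo rate is now expected to be no more than 40% instead of 60%, so the size needs another look. Section 12.8.2 states that, with at least 100 subjects, "data for the humoral immune response to Tat will be used to re-calculate the sample size", using the section 12.6 definition of a responder. Section 12.8.3 gives the safeguard for the blind: "An independent statistical vendor, who will not be involved in the final statistical analysis, will perform the sample size re-calculation". Section 12.8.5 then dismisses any effect on the error rate: "Since no formal treatment group comparison will be performed on the humoral immune response data, it will not be necessary to adjust" for inflation of the overall Type I error.

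**The concern.** The reason in 12.8.5 treats an interim hypothesis test as the only route to inflation. There is a second route. Suppose the final N is chosen from the observed difference and all data then go into one ordinary chi-square. The weight of the first stage in that statistic then depends on what the first stage showed. If a large chance difference cuts N from 100 to 60 per arm, the first 50 make up 50/60 = 83% of the data instead of 50/100 = 50%, so the chance finding is diluted less than planned. If a moderate difference raises N, the second stage gains weight just where it helps most. The statistic no longer has its nominal distribution under the null, although nobody looked at a p-value.

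At stake is the 5% two-sided level of the trial's one primary comparison. The protocol asserts it for a reason that does not secure it.

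**Working it through.** **1. The plan's own figure.** Inputs from section 12.3: 0.80 against 0.60, two-sided alpha 0.05, power 80%.

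n = [1.960·√(2·0.7·0.3) + 0.842·√(0.8·0.2 + 0.6·0.4)]² / 0.2² = (1.270 + 0.532)² / 0.04 = 81.2, so 82 per arm.

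With the continuity correction of the method cited in 12.3: n' = (81.2/4)·[1 + √(1 + 4/(81.2·0.2))]² = 90.95, so 91 per arm. This reproduces the stated 91.

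**2. Which rates enter the re-calculation?** The text does not say. Three features point to rates by arm: the trigger in 12.8.1 is an arm-specific rate, the sizing formula takes two arm rates, and pooled masked data would hardly need an independent vendor. No sentence in section 12.8 restricts the calculation to pooled data or holds the difference fixed.

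**3. Alpha if both arm rates are used.** The first stage is 50 per arm (half of the minimum 100). Both arms have the same true rate, in the range 0.2 to 0.8. N per arm is re-set by the formula above at the observed rates, bounded by a floor and a cap. All data are then tested with the uncorrected two-sided chi-square. No interim test is made. The protocol gives no numerical floor or cap, so those below are assumptions. The protocol also does not say what happens when placebo is ahead at the interim, so two conventions are shown.

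| N per arm (assumed floor-cap) | Wrong-direction interim sends N to the cap | N depends on the size of the difference only |
|---|---|---|
| 75-100 and 90-100 | 5.2-5.5% | 5.3-5.6% |
| 50-100 | 5.4-5.5% | 5.7-5.8% |
| 100-200 (increase only) | 5.4-5.6% | 5.9-6.1% |
| 50-300 | 5.9-6.0% | 6.9-7.0% |

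The third row was sized without the continuity correction, which matters little: without it, the 50-100 row becomes 5.6% and 6.0%.

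**4. Comparators under the same set-up.**
- Fixed 100 per arm: about 5.1%, so the chi-square is slightly above 5% even without re-sizing.
- Re-sizing on the pooled rate with the difference held at 20 points: about 5.0-5.2%.
- Re-sizing on the observed placebo rate alone, with the vaccine rate held at 80%: about 4.8-5.5%, though one run reached 5.7% at a common true rate of 0.7.
- Re-sizing by arm with an inverse-normal combination at fixed weights 0.5/0.5: 5.05-5.13%, against 5.65-7.13% for the ordinary chi-square under the same rules.

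**5. Direction of the change.** At the protocol's revised expectation, 80% against 40%, the formula gives [1.960·√(2·0.6·0.4) + 0.842·√0.40]² / 0.4² = 22.3, or 28 per arm with the continuity correction. That is below the 50 per arm already in the interim. The plan's own outlook is therefore a decrease, which makes the rows capped at 100 the more relevant ones. Nothing in section 12.8 rules out an increase.

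**The case against.** The strongest reply is that no sentence says the rates are taken by arm. Section 12.8.5 itself denies a formal group comparison, section 5.6 keeps study personnel blinded until database lock, and section 6.5 limits un-blinding to study end or emergencies. A pooled calculation fits that text, and under it the conclusion of 12.8.5 is right. This stands, and it is why the point is conditional. It does not rescue the reason given. The valid justification would be that re-sizing uses pooled data with a fixed difference, and the protocol never says so.

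A second reply is that only the placebo rate is in doubt, so the vaccine rate may be held at 80%. Then the excess is small for most true rates. This also stands, but the protocol does not state that rule either.

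Third, the larger figures need room that the plan may not give. Section 12.8.1 keeps everyone already consented and vaccinated, and enrolment is not paused, so the real floor probably exceeds 50 per arm. Caps of 200 and 300 appear nowhere. This stands, and it puts the excess over the fixed design in the more likely cases at a few tenths of a percentage point. A continuity-corrected chi-square would be conservative (3.8-4.8% by arm, 3.6% fixed), but section 12.6 names the plain test.

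Last, the re-sizing rule and its limits may sit in a SAP or interim plan that is not shown. Their absence is therefore no part of this point. The invalid reason is in the protocol itself.

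**Conclusion.** The reason in section 12.8.5 is wrong as written. Not testing at the interim does not protect the level when the final N depends on the observed difference between arms. If both arm rates are used, two-sided alpha is about 5.2-5.8% with N at or below 100 per arm, 5.4-6.1% if N may only rise from 100 to at most 200, and 6-7% with floor 50 and cap 300, against about 5.1% for a fixed 100 per arm. These figures rest on 50 per arm at the interim, the section 12.3 formula and assumed floors and caps. The lower end of each range takes wrong-direction interims to the cap.

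A reader might infer that the protocol prescribes arm-specific re-sizing and that this trial's Type I error is therefore inflated, perhaps to 7%. The documents do not support that. By-arm use is strongly implied but never stated, pooled use would leave the level at about 5.0-5.2%, and the 7% needs a cap found nowhere in the protocol. The point is a faulty assurance with a modest likely effect, and it should be corrected before the re-calculation is done.

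**What to change.** Replace the reason in 12.8.5 and add one rule to 12.8.2, choosing between:

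- **(a) Blinded re-sizing.** State that only the pooled, blinded responder rate is used, with a pre-fixed difference such as the 20 points of section 12.3, and that the ordinary chi-square is kept. Section 12.8.5 can then rightly say that no adjustment is needed. The cost is that neither the observed placebo rate nor the observed difference can drive the new size, although the placebo rate is what prompted the interim.
- **(b) Arm-specific re-sizing.** State that arm rates are used, give a minimum and maximum N, and make the final test an inverse-normal combination of the two stages with weights fixed in advance. The cost is a less familiar test statistic, and section 12.6 must change to match.

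Either choice is a change of wording only and needs no extra data.
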